##### Third round

In the third-round survey, participants who completed round two will be presented with outcomes from round two that were rated based on the consensus criteria outlined in Table 1. Participants will be asked to re-rate the retained outcomes using the same 9-point Likert scale. At the end of both surveys, unique outcomes meeting the consensus criteria (Table 1) (i.e. outcomes classified as “consensus in” and neither “consensus in” nor “consensus out”) will be brought for discussion at consensus meeting(s) with a global representative of stakeholders (parents/caregivers, healthcare providers and researchers) to decide on the final COS.

### Recruitment

Purposeful sampling will be used to ensure that those with opinions or known expertise in neonatal encephalopathy in both low-to-middle-income and high-income countries will inform this study. The target sample (parents/caregivers, healthcare providers and researchers with expertise in neonatal encephalopathy) will be accessed through invitational emails, electronic discussion lists, those who have participated in previous work or research in this area and other experts in neonatal encephalopathy who have published on neonatal encephalopathy as identified in the systematic review and qualitative interviews, through professional organisations, and support networks. Each organisation will be sent an email containing an information leaflet and an invitation to participate in COHESION (Additional file 1), which they will be asked to circulate to potential participants using their usual means of communication, i.e. mailing lists, website and social media activities. The email invitation will have an electronic link attached that will enable participants to register to participate and seek their consent. Participants will only be able to start the survey after they have given consent. Participants will be allocated randomly to a traditional, three-round Delphi survey or a Real-Time Delphi survey.

### Randomisation

We will use stratified randomisation of stakeholders (parents/carers, healthcare providers and researchers) on a 1:1 ratio. The randomisation sequence is generated using a computerised random number generator. This is based on the stakeholder’s unique identifier value which is generated by stakeholders selecting which stakeholder category they belong to in an initial demographic survey (i.e. parent, caregiver, neonatal nurse practitioners, midwives, obstetricians, neonatologists/paediatricians, neonatal/paediatric neurologists, general practitioners who provide long-term care for children with neonatal encephalopathy, policymakers and other healthcare providers such as therapists (speech, physical, etc.), etc.), and researchers with expertise in neonatal encephalopathy treatment. Based on their stakeholder category, participants will be grouped into three stakeholder groups (parents/caregivers, healthcare providers and researchers). Once the participant has clicked the survey link, they will be provided with access to the study information and Participant Information Leaflet. They will then be asked to click, within the survey, to provide consent. Demographic information will be collected, and the participant will be randomised within the survey platform. The user is automatically directed to the Multi-Round or Real-Time Delphi survey, based on their random allocation stratified for each of the three stakeholder groups in each survey arm.

Participants in both study arms will be able add comments and additional outcomes and we will compare how often this feature was used in the two arms. We will also ask participants in a short questionnaire, sent by email to those who completed each survey, how they found answering each survey, using a modified USE (Usefulness, Satisfaction and Ease of use) questionnaire [13, 14].

### Outcomes

#### Primary

We will compare the lists of outcomes at the end of both the Real-Time (week 5) and Multi-Round Delphi processes (week 14), and how the outcomes were rated based on the consensus criteria in Table 1.

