### Objectives

To identify whether different outcomes are prioritised when using a Multi-Round compared with a Real-Time Delphi method in the development of a COS for interventions for the treatment of neonatal encephalopathy.

The unique outcomes identified at the end of both survey arms will be brought forward to consensus meetings. At these meetings, the most important outcomes will be prioritised by key stakeholders (parents/caregivers of infants diagnosed and treated for neonatal encephalopathy, healthcare providers and researchers). An online discussion and final vote will be used to decide on which outcomes should be included in the final COS for the treatment of neonatal encephalopathy.

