##### Second round

The second-round survey will contain all outcomes from round one. Any new outcomes suggested by participants of the Multi-Round Delphi survey will be reviewed by a subgroup of the COHESION Steering Group, as in the Real-Time Delphi. Unique outcomes in the Multi-Round Delphi will be incorporated into the survey in the second round. Additional outcomes suggested in either survey arm will only be added to that survey arm (i.e. unique outcomes suggested by participants in the Multi-Round Delphi will not be incorporated into the Real-Time Delphi, and vice versa). The rating and consensus results will be based on the consensus criteria outlined in Table 1. Results from round one of the survey will be presented as the proportion of participants rating each outcome on each of the points in the 1 to 9 Likert scale, by each stakeholder group, as well as the overall consensus score. Results will be presented graphically and numerically. Participants will be given the opportunity to re-score the outcomes from round one based on (a) their individual score from the first round of the survey (b) results from each stakeholder group and (c) the consensus results overall for that outcome. In addition, participants will be asked to rate, for the first time, the additional outcomes that may be introduced following round one.

**Table 1 Tab1:** Consensus classification

Consensus classification	Description	Definition
Consensus in (parent/caregiver-weighted vote)	Consensus that the outcome should be included in the core outcome set	70% or more participants overall scoring as 7 to 9 AND < 15% participants scoring a 1 to 3 OR > 70% or more of parent group scoring as 7 to 9
Consensus out	Consensus that the outcome should not be included in the COS	50% or fewer participants scoring as 7 to 9 in each stakeholder group
Neither consensus in nor consensus out (undetermined consensus)	Uncertainty about the importance of the outcome so retain for next round	Anything else

Once again, participants will be asked to rate the outcomes using a 9-point Likert scale. Participants will also be asked of their willingness and availability to attend the subsequent consensus meetings.

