### Sample size

Although there is a lack of evidence-based guidance for the optimal sample size for each group participating in the Delphi survey, we aim to recruit a minimum of 180 participants overall (minimum of 30 per each of three major stakeholder group categories, i.e. parents/caregivers whose infants have been diagnosed with or treated for neonatal encephalopathy, healthcare providers and researchers with expertise in neonatal encephalopathy treatment) for each Delphi survey (i.e. 90 participants in the Multi-Round Delphi survey and 90 participants in the Real-Time Delphi survey) and retain participants using the retention methods as described.

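### A mismatch between the two arms' Table 1 lists cannot by itself answer the objective, because two samples of about 90 classified by hard cut-offs will disagree on some outcomes by chance

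*Protocol article*

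**What the plan says.** The Objectives section poses a comparative question: "To identify whether different outcomes are prioritised when using a Multi-Round compared with a Real-Time Delphi method". The Primary outcome subsection answers it by comparing the lists from the Real-Time arm (week 5) and the Multi-Round arm (week 14), and "how the outcomes were rated based on the consensus criteria in Table 1".

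Table 1 (under Second round) sorts each outcome into one of three classes:

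- *Consensus in* needs "70% or more participants overall scoring as 7 to 9 AND < 15% participants scoring a 1 to 3", or alternatively more than 70% of parents scoring 7 to 9.
- *Consensus out* needs 50% or fewer scoring 7 to 9 in every stakeholder group.
- Everything else is undetermined.

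The Sample size section plans "90 participants in the Multi-Round Delphi survey and 90 participants in the Real-Time Delphi survey", with a "minimum of 30 per each of three major stakeholder group categories" in each arm. Randomisation is 1:1 and stratified by stakeholder group.

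**The concern.** Each arm's list is an estimate from a random half of the participants. A percentage close to 70% or 50% can fall on either side of the cut-off through the draw of participants alone, and the parent route to *consensus in* rests on about 30 people. Two arms using the same method would still produce somewhat different lists.

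The primary outcome, as worded, gives the reader no way to separate that background disagreement from an effect of the Delphi method. The Secondary outcomes section does state null hypotheses for the feedback, initial condition and iteration effects, and regression equations for the first two. At stake is the trial's main message: ordinary sampling disagreement could be reported as a difference between methods.

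**Working it through.** **1. The plan's own figure.** 2 arms × 3 stakeholder groups × 30 = 180, which matches "we aim to recruit a minimum of 180 participants overall". It is a recruitment minimum with no error rate or effect size behind it.

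**2. Precision at the cut-off.** The standard error of a proportion is √(p(1−p)/n). At p = 0.70:

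- overall, n = 90: √(0.7 × 0.3 / 90) = 0.048, or 4.8 percentage points
- parents, n = 30: √(0.7 × 0.3 / 30) = 0.084, or 8.4 points

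For the difference between two independent arms, multiply by √2: about 6.8 and 11.8 points.

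**3. Chance discordance by simulation.** Both arms draw 30 + 30 + 30 independent ratings from the same true proportion scoring 7 to 9, and Table 1 is applied to each arm. There were 200,000 simulated outcomes per scenario. The document does not give the following, so they are assumptions:

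- the spread of true proportions across outcomes (varied as in the table)
- the share of the remaining ratings falling in 1 to 3 (20-40%)
- differences between stakeholder groups (logit SD 0 or 0.5)

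| Assumed true proportions | Outcomes classified differently by chance |
|---|---|
| Uniform 0.3-0.95 | 21-22% |
| Uniform 0.4-0.95 | 20-22% |
| Uniform 0.5-0.9 | 19-20% |
| Beta(7,3), mean 0.7 | 19-21% |
| Beta(4,2) | 19-20% |
| Uniform 0-1 | 14-15% |
| Beta(3,1) | 13-14% |
| Beta(8,2) | 11% |
| Bimodal, about 0.9 and 0.3 | 6-9% |
| Beta(9,1) | 3% |

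With 20 counted per group, the scenarios near 20% rise to about 22-26%. Table 1's AND/OR can also be read so that the 70% overall rule is always required. That reading lowers the mid-range scenarios to about 16-20%.

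**4. Where it arises.** For a single outcome, with the three groups alike, chance discordance is about 50% at a true proportion of 0.68 (in/undetermined boundary) or 0.45 (out/undetermined boundary). It is about 1% at 0.80 and essentially zero from 0.85.

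**5. Carried forward or not.** The Third round section sends both *consensus in* and undetermined outcomes to the consensus meeting, so only the *consensus out* boundary matters there. Chance discordance on that two-way split is at most about 11% in these scenarios with 30 per group.

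**6. At least one mismatch.** Assume 60 outcomes, independent of each other. At 3% discordance, 1 − 0.97^60 = 84%. At 11%, 1 − 0.89^60 exceeds 99.9%. With 30 outcomes, 1 − 0.97^30 = 60%.

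**7. Effect of feedback.** Independent ratings are a simplification. If feedback pushes outcomes away from the cut-offs (logit spread × 1.5 to 3), the spread and mid-range scenarios fall to 8-17%. If each arm drifts on its own (logit SD 0.3-0.5), they rise to 29-39%, and Beta(9,1) rises to 5-8%.

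**The case against.** The strongest reply is that this is a condensed article. An agreement statistic or test may sit in an analysis plan that is not shown, and the protocol nowhere says that any mismatch counts as a method effect. That is fair. It rules out two inferences a reader might draw: that no such analysis exists, and that the trial will almost surely declare a difference. What stands is narrower. The endpoint as worded is a list comparison, and a list comparison alone cannot answer the stated objective.

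A reader might also take one outcome in five as the expected noise. The document does not support a single figure. That value needs true proportions spread across, or centred near, the cut-offs; if ratings bunch high it falls to 3-11%.

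Nor does every mismatch alter the core outcome set. In-versus-undetermined differences do not change what an arm sends to the meeting, which is why the two-way figure is lower. The classification itself is still part of the primary outcome.

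Finally, first ratings may look like a ready-made null because feedback follows the first rating of an outcome. They are not a valid one:

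- In the Real-Time arm, feedback appears item by item, so later first ratings are made after seeing others' views on earlier items.
- Final ratings count only for those completing all rounds (Multi-Round) or for outcomes rated at least twice (Real-Time), as set out under Data collection methods.
- The spread around the cut-offs can change between first and final ratings.

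**Conclusion.** The point holds in this form: with about 90 per arm and hard cut-offs, identical methods would still give some discordant classifications, so a mismatch alone does not show that the method matters. Assuming independent ratings, the expected share is about 19-22% for mid-range true proportions and about 3-26% across plausible distributions with 20-30 counted per group. It is at most about 11% for carried forward or not with 30 per group. These figures rest on rating distributions that the document does not give.

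Even the low end is not negligible if any mismatch is read as a difference, since 3% over an assumed 60 independent outcomes gives an 84% chance of at least one. Two stated rules add to the problem. The counting rules can bring the analysed number below 90 per arm, and outcomes suggested by participants enter only the arm that suggested them, so the lists can differ for reasons other than rating. The plan should be changed, but the design and data collection need not be.

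**What to change.** Keep the list comparison and add the following to the primary analysis:

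1. Restrict the primary comparison to outcomes presented in both arms. Report outcomes added in one arm separately.
2. For each common outcome, give the between-arm difference in the percentage scoring 7 to 9, stratified by stakeholder group, with a 95% confidence interval.
3. Report the number of discordant classifications, and kappa, against their distribution when participants are re-allocated to arms at random within stakeholder strata.
4. State that this reference covers sampling noise only. Participants in an arm share one feedback stream, so an arm may drift as a whole. Exceeding the reference is necessary but not sufficient evidence of a method effect.
5. Show discordance of first ratings as descriptive context only, not as the null.

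The cost is a few sentences in the protocol or analysis plan and a short resampling program, with no new data. The downside is a little more analysis and a more cautious headline.

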#### Secondary outcomes

We will compare the outcomes that are prioritised (based on Table 1), from each survey arm, against the final COS.

Additional secondary outcomes are informed by previous comparison of Multi-Round Delphi method and the Real-Time Delphi method by Gnatzy et al. [8]:
2.*Feedback effect*

We will calculate the “feedback effect”, which will inform if, and how, the feedback provided to participants resulted in them amending how they rated an outcome. In the Multi-Round Delphi, participants will be given time (1 week) to process the feedback before the next round, where they can re-rate the outcomes. In contrast, in the Real-Time Delphi, participants will be provided with feedback in real-time. They will be given the option to change their rating or keep their answer the same before moving on to the next outcome. To estimate the feedback effect, we will test the null hypothesis:H0_1_: There is no difference in how participants react to feedback in both survey arms

We will use the following model to estimate this effect:
$$ {cor}_{kl}={b}_o+{b}_1\ast {dev}_{kl}+{b}_2\ast \gamma k+{b}_3\ast \left(\gamma k\ast {dev}_{kl}\right) $$*k*: participants of both Multi-Round and RT Delphi surveys*l*_s_: the projection dependent on *s* which indicates whether the projections (outcome rating) are from the Real-Time (*s* = 1) or Multi-Round (*s* = 2) Delphi study.cor_*kl*_ will indicate how strongly the *expected-probability (EP) values* were corrected after feedback was given.Dev_*kl*_: how strongly a stakeholder deviated from the final expected-probability value.γk∈{0, 1}: an indicator variable which takes on the value 1 if the expert *k* belongs to the Real-Time and 0 if an expert belongs to the Multi-Round Delphi study.*b*_1_: slope coefficient*b*_2_: indictor variable*b*_3_: interaction term3.*Initial condition effect*

To ensure that the first participant of the Real-Time Delphi survey is provided with feedback, a representative group of stakeholders (five of each parents/carers, healthcare providers and researchers) will vote on the importance of the outcomes (i.e. “initial conditions”) before the survey goes live to the public. These “initial conditions” may have an impact on how outcomes are rated subsequently during the survey process; we call this the “initial condition” effect. In addition, it may be suggested that participants engaging later in the survey have a greater level of feedback than early participants. This might influence how outcomes are re-rated. To identify if the initial conditions effect the final list of outcomes, we will test the hypothesis:H0_2_: There is no effect of the initial conditions on the outcomes that emerge as important at the end of the Delphi survey.

We will conduct a regression analysis with initial conditions and final results. The initial conditions will be the independent variable and final results will be the dependent variable. Furthermore, we will test whether the initial conditions cause participants to change their rating on outcomes compared to late participants. For this, we will use a linear regression model.
$$ {\mathrm{cor}}_{ij}={\beta}_0+{\beta}_1\ast {\mathrm{dev}}_{ij}+\beta 2\ast {\upvarphi}_i+{\beta}_3\ast \left({\upvarphi}_i\ast {\mathrm{dev}}_{ij}\right) $$*i*: participants in the Real-Time Delphi survey*j*: the projection (outcome rating)cor_*ij*_: how strongly the stakeholder’s *EP* assessment was altered after proving feedbackdev_*ij*_: how strongly a stakeholder differed from their *EP* valueφ_i_ ∈{0,1} represents an indicator variable where the value is 1 if the stakeholder *i* is an early participant (week 1) or 0 if the stakeholder is a late participant (week 4).

This model was developed by Gnatzy et al. [8] predicts how the deviation from average EP impacts corrections whilst accounting for possible differences between early and late respondents.
4.*Iteration effect*

In a Multi-Round Delphi survey, participants can only re-rate the outcomes in the second and third rounds. However, in the Real-Time Delphi, participants have the opportunity to re-visit the survey and re-rate the outcomes as many time as they wish. This difference in the iteration (“iteration effect”) could impact the consensus process.

We will compare any changes in standard deviation (SD) of the EP in both survey arms to test the hypothesis that:H0_3_: There is no difference in the consensus process between the Real-Time Delphi and the Multi-Round Delphi surveys.

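### The two printed feedback models omit the stakeholder group used to stratify randomisation, so group mix can pass for an early-versus-late effect and, if retention is unequal, for an arm effect

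*Protocol article*

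**What the plan says.** All references are to the Protocol article.

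- **Randomisation:** "We will use stratified randomisation of stakeholders (parents/carers, healthcare providers and researchers) on a 1:1 ratio". Participants are directed to a survey "based on their random allocation stratified for each of the three stakeholder groups in each survey arm". The group is recorded before allocation.
- **Secondary outcomes, feedback effect (H0_1):** "We will use the following model to estimate this effect". The equation regresses the correction (cor) on the deviation (dev), an arm indicator (b2) and arm x dev (b3).
- **Secondary outcomes, initial condition effect:** "For this, we will use a linear regression model". Within the Real-Time arm, cor is regressed on dev, an indicator equal to 1 for week-1 and 0 for week-4 participants (beta2), and their product (beta3). The model is described as "accounting for possible differences between early and late respondents". The test is framed causally, as whether initial conditions bring about re-rating.
- **Data collection methods:** Multi-Round ratings count only from participants who complete every round. A Real-Time rating counts if the outcome was rated at least twice.
- **Sample size:** a "minimum of 30 per each of three major stakeholder group categories" in each survey, giving "90 participants in the Multi-Round Delphi survey and 90 participants in the Real-Time Delphi survey".

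Neither equation has a stakeholder term, and no other section adds one.

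**The concern.** Stakeholder group is the stratification factor and is known for every participant, yet both regressions ignore it. The consequences differ.

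**Early versus late.** Nobody is randomised to enter in week 1 or week 4. If the groups enter at different times and also react differently to feedback, beta2 and beta3 partly measure who entered when. A significant result could then be read as an effect of the initial conditions when it reflects group composition.

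**Arm comparison (H0_1).** Stratified 1:1 allocation balances the groups at entry, so omitting group does not bias b2 or b3 at that point. Two smaller matters remain. Between-group variance stays in the residual, which costs some precision. And the counting rules differ by arm, so the group mix among counted ratings may differ between arms even though the randomised mix did not.

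**Working it through.** **The plan's own figure.** 30 per group x 3 groups x 2 arms = 180, as stated. The protocol gives no power calculation, variance, number of outcomes or between-group difference for these regressions, so everything below is illustrative.

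**Assumptions.**
- *Set A:* two-sided 5%, 50 outcomes per participant, residual SD 1, dev SD 1.5, group intercepts +0.4/0/-0.4 and slopes on dev +0.15/0/-0.15, between-participant SD 0 or 0.4, no true arm or early/late effect, 400 simulated data sets per scenario.
- *Set B:* participant slopes with SD 0.25 within group, and parents' mean slope higher by 0.1, 0.2 or 0.3.

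**Step 1: bias by hand.** With dev centred at zero and distributed alike in all groups, omitting group gives approximately

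false main effect = sum over groups of (share where indicator = 1 minus share where indicator = 0) x group intercept,

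and the same with group slopes for the interaction.

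- *Early 10/10/20, late 20/10/10, Set A.* Main effect: (10-20)/40 x 0.4 + (20-10)/40 x (-0.4) = -0.200. Interaction: the same shares with 0.15 give -0.075. Simulated: -0.197 and -0.076.
- *Milder mix, early 14/14/12, late 12/14/14.* 2/40 x 0.4 x 2 = +0.040 and 2/40 x 0.15 x 2 = +0.015. Simulated: +0.041 and +0.015.
- *Strong mix, small group differences (intercepts +/-0.1, slopes +/-0.05).* -0.050 and -0.025. Simulated: -0.049 and -0.025.
- *Arm comparison, counted 27/27/27 in Real-Time and 18/24/27 in Multi-Round.* Multi-Round mean intercept: (18-27) x 0.4/69 = -0.052, so false b2 = +0.052. Slopes: (18-27) x 0.15/69 = -0.020, so false b3 = +0.020. Simulated: +0.052 and +0.019.
- *Arm comparison, balanced 30/30/30.* All share differences are 0. Simulated: +0.002 and +0.001.
- *Set B, early 6/17/17, late 12/4/4.* Parent share 0.15 minus 0.60 = -0.45, so false beta3 = -0.045, -0.090 or -0.135.

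**Step 2: what removes the bias.** With group and group x dev added, every Set A mean was within 0.005 of zero. A group main effect alone corrected beta2 but left beta3 at -0.075 in the strong early/late mix, so the product term is needed.

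**Step 3: error rates.** Strong early/late mix, Set A, between-participant SD 0.4, nominal 5%:

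| Model | Standard errors | beta2 rejects | beta3 rejects |
|---|---|---|---|
| As printed | ordinary | 92% | 88% |
| As printed | clustered by participant | 36% | 55% |
| + group, group x dev | ordinary | 44% | 5% |
| + group, group x dev | clustered by participant | 8% | 5% |

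Across all Set A scenarios, adjusted models with participant-clustered standard errors rejected 3-8%. With 400 runs, the Monte Carlo standard error of a true 5% is 1.1 points.

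Set B makes the same point for the interaction. Fitted to individual ratings with ordinary standard errors, the balanced H0_1 test of b3 rejects 28-30% (20 outcomes each) or 43-51% (50 outcomes) without group, and 27-31% or 43-50% with it. If each participant is reduced to one slope, so that clustering is handled, the unadjusted early/late rates for 6/17/17 v 12/4/4 are 9, 21 and 40%, and the adjusted rates are about 5%.

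**Step 4: precision for H0_1.** In Set B, with one third parents, group explains d² x (1/3)(2/3) / [d² x (2/9) + 0.25²] of the slope variance: about 3%, 12% and 24% for d = 0.1, 0.2 and 0.3. With clustering handled, adjustment moved power from 81 to 82%, 80 to 84% and 82 to 89%.

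**The case against.** The strongest reply has four parts.

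*No evidence that groups differ in the relevant way.* Feedback is shown by stakeholder group and Table 1 gives parents their own route to consensus. A reader might infer that the plan expects groups to react differently. It shows only that they may rate differently. The models concern movement at a given deviation, on which the protocol is silent. Likewise, the Recruitment section lists channels jointly and gives no entry times, so it does not show that parents enter later than professionals. This stands: the confounding is possible, not demonstrated.

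*The arm test is not conservative as printed.* A reader might infer that stratifying and then ignoring the strata makes the H0_1 test too cautious. That holds only once clustering is handled. With ordinary standard errors on individual ratings, Set B gives heavy over-rejection with or without group. This also stands.

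*Covariates belong in the analysis plan.* An analysis plan may add them. But the protocol prints the regressors of both models, so this is a stated choice and not an omitted detail. That the models come from an earlier comparison is no answer: by the protocol's own account its participants were not randomised, so it had no randomisation strata to respect.

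*Limited reach.* Both models are secondary, and the early/late model is one part of the initial-condition analysis within one arm. This stands and limits the weight of the point.

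**Conclusion.** The point holds in a limited form. Both printed models leave out a recorded stratification factor. In the early/late model, group is a potential confounder of a non-randomised contrast that is given a causal reading. In the arm model, allocation protects against group-mix bias at entry. The case for adjustment there is a small gain in precision (1 to 7 points of power under the assumed differences) and insurance against unequal counting. The counting rules make unequal group mixes possible, but nothing in the protocol says that retention will differ by group.

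The size cannot be fixed from the documents. It grows with both the imbalance in mix and the difference in reaction, and is nil if either is absent. It would be wrong to conclude that adding group makes the tests valid: adjusted rates near 5% apply only when repeated ratings per participant are also accounted for. The primary comparison of outcome lists is untouched.

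**What to change.** In both equations under Secondary outcomes, add stakeholder group (three levels, as randomised) and group x dev. Test b2 and b3, and beta2 and beta3, from these adjusted models, with dev centred so that the main effects are interpretable. Keep the models as printed as sensitivity analyses. State also how repeated ratings by one participant are handled, for example with participant-clustered standard errors, since the group terms do not do this.

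The cost is two group indicators and two products, so four coefficients per model and a few degrees of freedom. No new data are needed, and by the Trial status section recruitment has not begun.

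### The feedback-effect and early/late regressions have nothing to account for repeated ratings by the same person, so row-based standard errors for arm, entry week and their interactions with deviation are too small whenever a person's ratings are correlated.

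*Protocol article*

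**What the plan says.** In the protocol article, Secondary outcomes, item 2 (Feedback effect), the null hypothesis is "There is no difference in how participants react to feedback in both survey arms". The article continues "We will use the following model to estimate this effect" and prints cor_kl = b0 + b1·dev_kl + b2·γ_k + b3·(γ_k·dev_kl). Here k is the participant, l the outcome rating, and γ_k is 1 for Real-Time and 0 for Multi-Round.

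Item 3 (Initial condition effect) first regresses final results on initial conditions. It then adds a comparison of early with late Real-Time participants: "For this, we will use a linear regression model". That equation has the same form, cor_ij = β0 + β1·dev_ij + β2·φ_i + β3·(φ_i·dev_ij), with φ_i equal to 1 for week 1 and 0 for week 4.

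Neither equation has a participant term, and neither is accompanied by an error structure or a variance correction. The Real-Time and Multi-Round method sections have every participant rate each outcome on the list. Under Randomisation, people are the units allocated: "We will use stratified randomisation of stakeholders (parents/carers, healthcare providers and researchers) on a 1:1 ratio".

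**The concern.** Both models have one row per participant and outcome. Arm and entry week take a single value for each person, so a further rating from the same person adds little information about them if that person's ratings move together. Such correlation is likely: some people revise readily and others hardly at all, and some follow the group more closely than others. A regression that counts rows treats these ordinary differences between people as if they averaged out over all rows.

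The risk is that chance differences between the people in the two arms, or between early and late joiners, are reported as an effect of the Delphi format or of entry time, with confidence intervals that are too narrow. The primary comparison has no stated hypothesis test, so these secondary models carry much of the article's formal inference about the two formats.

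**Working it through.** **The plan's own figure.** The article aims for "we aim to recruit a minimum of 180 participants overall", with a "minimum of 30 per each of three major stakeholder group categories" in each survey: 30 × 3 groups × 2 arms = 180, or "90 participants in the Multi-Round Delphi survey and 90 participants in the Real-Time Delphi survey". This reproduces. It is a recruitment target with no power, alpha or effect size, so there is no stated error rate to compare with.

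**Inputs.**
- From the article: the two equations, their indices, individual randomisation, and 90 participants per arm.
- Assumed because not given: two-sided 5% tests; m outcomes per person, 20 to 100; within-person correlation (ICC) of the correction given dev, 0 to 0.30; SD of individual slopes on dev, 0 to 0.3; 25 early and 25 late participants.

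**Arm or entry-week term (b2, β2).** For a covariate that is constant within a person:
- design effect DE = 1 + (m − 1)·ICC
- factor by which the row-based SE is too small = √DE
- true size of a nominal 5% test = 2Φ(−1.96/√DE)

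| m | ICC | DE | √DE | True size |
|---|---|---|---|---|
| 20 | 0.01 | 1 + 19 × 0.01 = 1.19 | 1.09 | 7% |
| 30 | 0.05 | 1 + 29 × 0.05 = 2.45 | 1.57 | 21% |
| 30 | 0.10 | 1 + 29 × 0.10 = 3.90 | 1.97 | 32% |
| 50 | 0.05 | 1 + 49 × 0.05 = 3.45 | 1.86 | 29% |
| 50 | 0.10 | 1 + 49 × 0.10 = 5.90 | 2.43 | 42% |
| 100 | 0.05 | 1 + 99 × 0.05 = 5.95 | 2.44 | 42% |
| 100 | 0.10 | 1 + 99 × 0.10 = 10.90 | 3.30 | 55% |
| 100 | 0.30 | 1 + 99 × 0.30 = 30.70 | 5.54 | 72% |

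The number of participants does not enter DE, so recruiting more people would not remove the problem.

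**Interaction (b3, β3).** The product γ_k·dev_kl changes from outcome to outcome within a person, so the formula above does not apply directly. The printed model was therefore simulated with no arm effect: 90 + 90 people, 600 replicates per scenario, residual SD 1, dev with SD 1.5 and an assumed within-person correlation of 0.2. It was fitted by ordinary least squares on rows and again with participant-clustered standard errors, for m = 30, 50 and 100.

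| Scenario | b3 SE too small by | b3 rejection, rows | b3 rejection, clustered |
|---|---|---|---|
| ICC 0, slope SD 0 | 1.00 to 1.03 | 4% to 6% | 5% to 6% |
| ICC 0.05, slope SD 0 | 1.16 to 1.46 | 10% to 19% | 4% to 7% |
| ICC 0.05 to 0.10, slope SD 0.10 to 0.15 | 1.45 to 2.77 | 17% to 48% | 5% to 7% |
| ICC 0.20 to 0.30, slope SD 0.20 to 0.30 | 1.98 to 4.47 | 31% to 65% | 4% to 7% |

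The second row can be checked by hand. With correlated levels only, the inflation is approximately 1 + (m − 1)·ICC·(correlation of dev within a person). At m = 100 this is 1 + 99 × 0.05 × 0.2 = 1.99, and √1.99 = 1.41, against 1.46 simulated. This mild effect therefore depends on dev itself being correlated within people.

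**Early/late model.** With the assumed 25 + 25 people and some within-person correlation, row-based rejection of the interaction was 9% to 16% without slope variation and 15% to 63% with it. Across both models, clustering gave about 3% to 7% for both terms.

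**The case against.** The strongest defence is that the equations give only the mean structure. Participant-clustered standard errors would leave every printed coefficient in place, item 2 does not name ordinary least squares, and an analysis plan that is not shown may specify the variance. It is true that independence is implied and not stated. But the article does not leave the model open: it prints every term and, in item 3, names linear regression, whose default standard errors count rows. Someone following the text would get the understated errors.

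Several stronger readings are tempting, and the documents do not support them.
- *The standard errors are several times too small.* The number of outcomes and the correlations are not given. The arm-term factor runs from 1.09 to 5.54 over the non-zero correlations tabulated, and is 1 with no correlation.
- *The interaction terms are constant within a person.* They are not, because dev is indexed by outcome as well. Large inflation for b3 needs people to differ in slope.
- *The iteration-effect test (H0_3) has the same inflated error.* Item 4 says only "We will compare any changes in standard deviation (SD) of the EP in both survey arms" and names neither a test nor a unit of analysis, so no error rate can be attached to it.
- *These are the only formal tests.* The first regression under H0_2 is a separate one, and H0_3 is also posed as a hypothesis.
- *The trial's main result is at risk.* The primary comparison of outcome lists does not use these models.

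**Conclusion.** The point holds for the two printed models. Followed as written, they understate the standard errors of the arm and entry-week terms whenever one person's ratings are correlated. They also understate those of the interactions: mildly with correlated levels alone, and more if people differ in how strongly they respond to deviation.

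For 30 to 100 outcomes and ICC 0.05 to 0.10, the arm or entry-week SE is about 1.6 to 3.3 times too small and a true null is rejected in about 21% to 55% of trials. For b3 the figures are about 10% to 19% without slope variation and 17% to 65% with slope SD 0.1 to 0.3. The top of that last range also assumes ICC 0.30 and 100 outcomes. The direction is secure given any positive within-person correlation in level or slope, with the dev condition noted above for b3. The size rests on assumptions. Only secondary analyses are affected.

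**What to change.** In Secondary outcomes, items 2 and 3, do one of the following:

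- fit a mixed model with a participant random intercept, a participant random slope on dev, and an outcome effect; or
- keep the printed equations and state that standard errors are clustered on participant, with a small-sample correction and degrees of freedom based on the number of participants. The correction matters most for the early/late model, which uses only part of one arm.

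The cost is a sentence or two of text and a few lines of code, with no extra data or participants. The downside is wider intervals than the printed models would give. The Trial status section says recruitment has not started, so the change can be made before any data are seen.
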